## Abstract

**Background:**

Anxiety is a common diagnosis in children with autism spectrum disorder (ASD). One key mechanism underlying anxiety is intolerance of uncertainty, which is a tendency to react negatively on an emotional, cognitive, and behavioural level to uncertain situations and events. We developed the first intervention programme specifically targeting intolerance of uncertainty in children with ASD: Coping with Uncertainty in Everyday Situations (CUES). CUES is a parent group intervention providing parents of children with ASD with strategies to increase tolerance to uncertainty for their children in everyday situations. The principal aims of the current study are: 1) evaluate the acceptability and feasibility of delivering CUES to parents who have a child with ASD and anxiety; and 2) inform the design of a fully powered trial.

**Method:**

This is a feasibility and acceptability single-blind pilot randomised controlled trial comparing CUES (intervention) to a brief psychoeducation, emotional literacy, and relaxation programme (enhanced services as usual). Participants will be assessed at baseline and followed-up immediately post-treatment, and at 12 and 26 weeks post-treatment. Parents who have a child with ASD and anxiety (aged 6–16 years) will be invited to take part in the study and written parental informed consent and child assent will be obtained. Participants will be recruited from the National Health Service mental health teams in the UK. Sixty participants will be randomised to either intervention or enhanced services as usual in a 1:1 ratio.

**Discussion:**

The present study will provide evidence on the acceptability of the CUES intervention to parents and children, and the feasibility of recruitment and delivery to inform the design and sample size for a full-scale randomised controlled trial. Qualitative data will be obtained to understand how feasible CUES is for families, and the experiences of participants regarding their experiences of the intervention.

**Trial registration:**

ISRCTN, ISRCTN10139240. Registered on 14 May 2018.

**Electronic supplementary material:**

The online version of this article (10.1186/s13063-019-3479-0) contains supplementary material, which is available to authorized users.

## Background

Mental health, and specifically anxiety, is amongst the top five research priorities for future autism spectrum disorder (ASD) research [1]. Approximately 50% of children with ASD experience high anxiety, congruent with an anxiety disorder [2, 3], which significantly impacts on everyday life for them and their families. Anxiety is a major risk factor for mental health difficulties in adulthood, including suicidal thoughts and behaviours [4]. When present, anxiety in individuals with ASD is often complex, encompassing features of a range of concurrent anxiety disorders, as well as atypical presentations [5, 6]. Therefore, treatment targeting the underlying mechanisms rather than specific symptoms is likely to be necessary and may be more effective. One key mechanism is intolerance of uncertainty (IU). IU is a ‘broad dispositional risk factor for the development and maintenance of clinically significant anxiety’ [7]. It involves the ‘tendency to react negatively on an emotional, cognitive, and behavioural level to uncertain situations and events’ [8].

Studies of people with ASD suggest that IU is a transdiagnostic construct associated with a range of anxiety disorders [9–13]. Importantly, intervention studies with neurotypical individuals suggest that a reduction in IU is associated with a reduction in anxiety and improvements in everyday functioning (see, for example, [14]). The role of IU in anxiety in typically developing adolescents [15–17] and children [18, 19] has been increasing, and it is argued that cognitive behavioural treatments, which emphasise treating the cognitive process rather than the cognitive content of anxiety, specifically by aiming to increase the tolerance of patients for uncertainty, achieve more sustainable change [20, 21]. Research has confirmed the utility of such protocols in reducing anxiety in adults and children without ASD [22–25].

Recently, IU has been associated with some of the core characteristics of ASD [26–28]. Restricted and repetitive behaviours, such as insistence on sameness, inflexible adherence to routines, and difficulty tolerating change, have been linked with anxiety in ASD since the earliest descriptions of the disorder [29] and bear a conceptual resemblance to IU; that is, avoidance of unexpected events and desire to make life as predictable as possible [30]. There is also evidence that IU has a central role in the relationship between ASD and anxiety. Boulter et al. [11] reported significant relationships between IU and anxiety in children with ASD, and their results suggested that, compared with matched neurotypical controls, IU levels account for the increased anxiety observed in children with ASD. Wigham et al. [10] examined the role that IU has in pathways between sensory processing difficulties, anxiety, and restricted and repetitive behaviours in ASD. These relationships were mediated by IU, indicating the important role IU may have in the interaction between anxiety and ASD traits. Chamberlain et al. [12] reported associations between shared neurobehavioural mechanisms in ASD and anxiety, indicating specific avenues for intervention targeting IU. Rodgers et al. [31] developed and validated a child self-report and parent-report measure of anxiety for children with ASD (the ASC-ASD). Using factor analytic techniques, Rodgers identified four reliable anxiety subscales, including an uncertainty scale. Hodgson et al. [32] undertook focus groups with parents of children with ASD exploring the concept of IU. Parents differentiated IU from dislike of change and from fear, discussed examples of IU and its impact on their children, and suggested that IU is a recognisable and important construct associated with anxiety distinguishable from but related to features of ASD. Although many of the studies come from the Newcastle group, in an independent multisite study Keefer et al. [9] demonstrated that high levels of pretreatment IU significantly predicted poorer treatment response in a group of children with ASD receiving treatment for anxiety. Neil et al. [33] further replicated that IU is a relevant construct related to sensory sensitivities and anxiety in children with ASD. Finally, Kerns et al. [34] in a discussion of the differential diagnosis of anxiety disorders in ASD report that fears associated with uncertainty may be an important mechanism in the development and maintenance of anxiety in ASD. In conclusion, this evidence indicates that IU appears to be an important mechanism in the development and maintenance of anxiety for children with ASD and an appropriate target for intervention.

Therefore, we developed the first intervention programme specifically targeting IU in children with ASD: Coping with Uncertainty in Everyday Situations (CUES) [5]. CUES is an 8-week parent group intervention that provides parents of children with ASD with strategies to increase tolerance of uncertainty for their children in everyday situations. Our CUES development project [5] provided preliminary evidence that CUES is feasible and acceptable to families, that parents found it helpful to work with clinicians to develop a range of strategies to tackle uncertainty in everyday contexts that they can support their child to utilise, and parents and children reported beneficial effects on everyday functioning. We now plan to conduct a feasibility and acceptability randomised pilot trial of CUES. The SPIRIT checklist is included as Additional file 1.

## Methods/design

### Trial design

This is a feasibility and acceptability pilot randomised controlled trial of a parent group-based intervention aimed at increasing tolerance to uncertainty in children with ASD: Coping with Uncertainty in Everyday Situations (CUES) [5].

### Aims

We aim to: 1) ascertain whether CUES is feasible to deliver through UK National Health Service (NHS) services by trained therapists, and is acceptable and well received by families; 2) establish the rate of referrals from child mental health teams in two NHS Trusts; 3) record the proportion of families who agree to participate and the proportion who complete all sessions, and to explore suitable methods of data collection and outcomes in relation to health services costs and costs to families of children with IU; 4) investigate whether treatment fidelity can be maintained across therapists; 5) record response rates for completion of outcome measures; 6) obtain participant feedback on the programme and valued outcome measures; 7) determine the acceptability/credibility of our active control group procedures; 8) investigate whether the families who participate in CUES have greater reduction in real-life IU and anxiety than children receiving enhanced services as usual; 9) describe variability in responses to CUES in children referred from NHS services; and 10) monitor whether any treatment effects persist 6 months post-treatment (primary endpoint).

### Setting and participants

Sixty parent participants will be recruited via NHS services (including diagnostic clinics and Child and Adolescent Mental Health Services). This number is based on recommendations for good practice in feasibility studies [35]. Parents are eligible for study entry if their child meets the following criteria: 1) a diagnosis of ASD; 2) aged 6–16 years; 3) experiences some anxiety; 4) no intellectual disability or mild-to-moderate intellectual disability; and 5) have sufficient language ability to complete appropriate outcome measures (with assistance if required).

Parents themselves will have sufficient spoken and written English to provide written informed consent, complete assessments, and participate in the intervention. Parents are not eligible for study entry if their child meets the following criteria: 1) no diagnosis of ASD diagnosis; 2) experiences severe and complex anxiety disorder (based on the clinical judgement of clinicians); 3) has severe intellectual disability; or 4) has complex health conditions.

Furthermore, children of parents who have significant mental health difficulties will not be eligible to participate.

### Participant identification and recruitment process

Families will be identified via NHS services. At NHS services, clinicians at the participating identification centres will be provided with information about IU to ensure familiarity with the construct to enable them to introduce the study to families. Clinicians will identify children fitting the inclusion criteria, discuss the study with them, and if interested give them study packs (Fig. 1). Interested parents will complete an expression of interest form that will be sent to the research team. The research team will then contact parents to arrange a face-to-face meeting to discuss the study, what participation involves, answer any questions they may have, and arrange written informed consent. Baseline data will be collected at this point, prior to randomisation.

**Fig. 1 Fig1:**
[figure not shown]
Participant identification, recruitment, and follow-up procedure. CUES Coping with Uncertainty in Everyday Situations, IU intolerance of uncertainty

Information provided to participants makes it clear that they do not have to participate in the trial and their decision will not affect their treatment. The participant can withdraw from the study at any time, which will not affect any further NHS treatment or services.

### Treatment

#### Intervention arm: CUES

CUES is an 8-week manualised programme [5] that provides parents of children with ASD the strategies to increase tolerance to uncertainty in everyday situations in their children. It was devised in partnership with parents. The key goal of the programme is to increase the child’s tolerance to uncertainty, reduce negative beliefs about uncertainty, and develop a more flexible approach to uncertainty. A parent-mediated intervention is appropriate because it provides parents with strategies that they can utilise with their child across a range of everyday contexts. It also supports generalisation of these strategies outside of the clinic setting, as well as countering well-meaning, understandable but ultimately unhelpful/counter-productive strategies used by parents to try to build certainty around the child, when certainty is not realistically possible. Thus, working with parents increases the translational potential of the intervention.

Parents will attend the programme, with two therapists with expertise in ASD facilitating each group. Each group will include approximately ten parents and sessions will take place weekly for 8 weeks. Each session will be 2 h in duration. ‘At home’ activities will be set each week for parents and children to complete between sessions. The programme begins with a focus on the development of understanding of uncertainty in everyday life, the nature and impact of IU, and promotes the use of strategies to flexibly manage IU across a range of settings. The intervention helps parents to recognise IU and identify potential developmental and environmental factors that may trigger IU for their child. It further teaches parents to plan and use appropriate strategies aimed at increasing their child’s tolerance of uncertainty. Each parent will be provided with weekly materials and individual support to identify strategies to address a chosen target IU situation. This target situation is the focus for parents to practise the new strategies with their child, thus ensuring that strategies are individually tailored for each child and are developmentally appropriate. The group situation provides extensive opportunities for mutual learning and support. The CUES intervention has incorporated and synthesised components of existing good practice in relation to anxiety treatment for children with ASD. It provides the opportunity for parents to develop an understanding of IU and its impact, to try out various strategies, and provides opportunities for discussion, mutual support and sharing of ideas, and experiences and strategies, importantly building parents’ knowledge and confidence to support their child at home to develop a more flexible approach to uncertainty.

Therapists delivering CUES are trained in the skills needed to deliver the programme through two training sessions (5 h in total). To ensure the intervention is being delivered as intended, with high fidelity to the manual, the principal investigator (JR) and the clinical lead (VG) will undertake supervision and monitoring of the quality of parent group sessions by video, providing timely feedback to group leaders. Weekly supervision of the therapists will be conducted by JR and VG. Treatment fidelity will be maintained and investigated from multiple standpoints, including supervisor feedback, and formally by observer ratings of recordings of the group sessions.

#### Enhanced services as usual arm: Understanding Autism

Understanding Autism will comprise two parent group sessions. Each session will be 2 h in duration. Parent group-based interventions provide parents with the opportunity not only to develop knowledge and skills in relation to the treatment target (in this case IU), but also provide opportunities for discussion, mutual support, and sharing of ideas, a process which parents tell us they value. Given the feasibility and acceptability aims of the current study, we were concerned that offering families in the control arm no opportunity to meet together as a group might significantly bias favourable responses in relation to acceptability towards the CUES intervention arm. In addition, treatment as usual is highly variable and thus the introduction of a two-session programme for the enhanced services as usual arm enables us to provide parents with some common content, and credibility/expectancy will be rated for both arms, whereas services as usual cannot be rated; this creates a greater level of equipoise than treatment as usual. There is currently no equivalent eight-session parent support group available to parents of children with ASD within this age range, and parents in the control arm receive a two-session Understanding Autism programme. This enables parents randomised to the control arm to have experience of a parent group setting. Both arms will continue to receive treatment as usual, which will be recorded on the demographics form.

The group will focus on psychoeducation, social communication, repetitive behaviours, and making and keeping friends. There are opportunities for parents to engage in group discussion regarding their experiences, such as the ASD diagnostic process.

Group leaders for Understanding Autism have extensive knowledge on ASD and have a track record of involvement in research and community outreach. The materials were developed in collaboration with the research team. They will receive weekly supervision with the principal investigator. Further, to ensure Understanding Autism is being delivered as intended (without reference to anxiety or IU), the principal investigator (JR) will monitor the quality of parent group sessions by video, providing timely feedback to group leaders. Fidelity will be formally assessed by an independent rater utilising a fidelity checklist and recordings of the group sessions. The control group will not have access to the intervention after the trial.

### Strategies to maintain adherence

A number of strategies will be utilised to improve adherence in terms of attendance at the intervention sessions and completion of the follow-up assessments. These includes written information about the venues for the sessions, in the case of absence from a session the materials for the session are posted to the participant to be received during the week of absence and a telephone call arranged between one of the therapists and the parents to ensure they have received the materials, determine if they have any questions, and encourage attendance at the next session. Parents are sent reminder emails, followed up with a telephone call if follow-up questionnaires have not been received. All parents receive regular newsletters about the study, along with seasonal greetings cards to encourage continued participation.

### Harm

Based on the development study for CUES [5] adverse events or unintended effects are not anticipated. However, if a clear safeguarding concern arises this will trigger an immediate response. The staff delivering the programmes are employees of the sponsoring Trust and will follow Trust protocols. In addition, therapists will receive weekly supervision from the principal investigator, on the same day as the intervention session takes place, and reporting of any unintended effects or adverse events is included as a standard item on the supervisory agenda. If any such events are identified, they will be discussed with the clinical lead which will result in action appropriate to the situation following the Standard Operating Procedures of the sponsor (Northumberland Tyne and Wear NHS Foundation Trust (NTW)), which are compliant with Good Clinical Practice (GCP) and Health Research Authority (HRA) guidelines for safety reporting. All such events will be recorded in the site file.

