
### Data collection and data management

Figure 2 details the information collected at different time points. To reduce burden for the family, follow-up assessments using questionnaire measures will be completed by post and the IU scenarios outcome measure will be rated by parents during follow-up telephone semistructured interviews with the blinded researcher. Northumberland Tyne and Wear NHS Foundation Trust may audit the data collected. Data collected on paper assessment tools will be entered onto a secure statistical analysis software system. A unique trial number will be used to identify participants on all paper data collection forms throughout the duration of the trial. No participant-identifiable data will leave the study site. The quality and retention of study data will be the responsibility of the principal investigator. All study data will be retained in accordance with the latest Directive on Good Clinical Practice (2005/28/EC) and local policy. Staff involved in the conduct of the trial, including the principal investigator, Trial Management Group and therapist staff involved in screening and intervention, will have access to the site files. Clinical information shall not be released without the written permission of the participant, except as necessary for monitoring and auditing by the Sponsor, its designee, regulatory authorities, or the REC. The principal investigator and staff involved in this trial may not disclose or use for any purpose, other than performance of the trial, any data, record, or other unpublished, confidential information disclosed to those individuals for the purpose of the trial.

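### The only routine adverse-event enquiry described runs through session-day supervision (8 occasions in CUES, 2 in control), and none is described for the 26 weeks after treatment

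*Protocol article*

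**What the plan says.** The Harm section of the protocol article expects no adverse events and describes how any would come to light. Safeguarding concerns are acted on at once, and staff follow Trust protocols. Beyond that, there is one routine route: "reporting of any unintended effects or adverse events is included as a standard item on the supervisory agenda". The supervision meant here is weekly, is given by the principal investigator and is held "on the same day as the intervention session takes place". Once an event is identified, it is discussed with the clinical lead, handled under the sponsor's procedures and entered in the site file.

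The number of session days differs by arm. For CUES, "Each group will include approximately ten parents and sessions will take place weekly for 8 weeks". For control, "Understanding Autism will comprise two parent group sessions". Of the control group leaders the article says "They will receive weekly supervision with the principal investigator", without repeating the adverse-event item.

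On follow-up, the abstract says "Participants will be assessed at baseline and followed-up immediately post-treatment, and at 12 and 26 weeks post-treatment". Under Data collection and data management, "follow-up assessments using questionnaire measures will be completed by post", and the target situations are covered in telephone interviews with the blinded researcher. No question about adverse events is described at any of these contacts.

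Under Planned analyses, minimal risk is one of the reasons given for having no data monitoring committee.

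**The concern.** The routine enquiry follows the sessions, and the sessions are part of what is randomised. The arm with more sessions has more scheduled occasions on which an event can be noticed and recorded, whatever the true rates are. When the sessions end, the scheduled enquiry ends in both arms, although outcomes are still sought to 26 weeks and persistence at 6 months is labelled the primary endpoint under Aims.

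Two other features point the same way. The weekly questionnaire on reactions to uncertainty is given only during CUES. Control sessions are monitored to keep anxiety and intolerance of uncertainty out of the content, so worsening anxiety has less chance of being mentioned there.

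Two uses of the trial are at stake. It should show whether the expectation of minimal risk is borne out, and it should tell the designers of a full trial which harms to collect and how. Counts gathered in this way can do neither reliably.

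**Working it through.** The article states no adverse-event rate or count, so there is no figure to reproduce. The check compares the opportunity for routine enquiry by arm and over time.

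**Inputs from the article**
- 60 families randomised 1:1, so 30 per arm (abstract).
- CUES: 8 weekly sessions of 2 h, about ten parents per group.
- Control: 2 sessions of 2 h.
- Follow-up to 26 weeks after treatment.

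**Assumptions**
- The agenda item applies to control group leaders as well.
- The two control sessions are a week apart.
- Control groups are the same size as CUES groups.
- Attendance is complete.

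**Step 1: scheduled occasions by arm**
- Per family: 8 / 2 = 4.0.
- Session hours: (8 × 2) / (2 × 2) = 16 / 4 = 4.0.
- Supervision occasions with 30 / 10 = 3 groups per arm: (3 × 8) / (3 × 2) = 24 / 6 = 4.0.
- If the item does not apply to control leaders, the comparison is 8 against 0.

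**Step 2: share of the study period covered by session-day supervision**
- CUES: 8 / (8 + 26) = 8 / 34 = 24%.
- Control, on its own clock: 2 / (2 + 26) = 2 / 28 = 7%. On the CUES clock: 2 / 34 = 6%.
- Both arms, each on its own clock: (30 × 8) + (30 × 2) = 300 family-weeks covered and 60 × 26 = 1560 not covered. The uncovered share is 1560 / 1860 = 84%.
- Scheduled enquiries described between the last session and week 26: none in either arm.

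**Step 3: what equal true risk would look like**

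Let p be the chance that a report arises at any one session, the same in both arms. The chance of at least one report per family is 1 − (1 − p)^8 in CUES and 1 − (1 − p)^2 in control. The article gives no value for p, so a range is shown.

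| p (assumed) | CUES | Control | Ratio |
|---|---|---|---|
| 0.01 | 7.7% | 2.0% | 3.9 |
| 0.02 | 14.9% | 4.0% | 3.8 |
| 0.05 | 33.7% | 9.8% | 3.5 |

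Across this range, CUES families would be 3.5 to 3.9 times as likely to have a report, with no difference in risk.

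**The case against.** The strongest reply is that the article has more safety cover than the supervision item. Four parts of that reply stand.

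- **Other routes exist.** A reader might infer that supervision is the sole means of detection. The Harm section does not support that: safeguarding and Trust protocols come first and are not confined to session weeks. They respond to concerns that arise, however, and are not a systematic enquiry.
- **Families who miss sessions or leave are contacted.** A reader might infer that nobody asks them anything. Absent parents are telephoned (Strategies to maintain adherence), and reasons for not completing are sought where possible (Planned analyses). These contacts concern materials, attendance and reasons; none is described as asking about harms.
- **Worsening is measured.** A reader might infer that the lower part of the nine-point scale is discarded because only the top 3 points are given a name. The article does not say so, and mean change is planned for all outcome measures. Anxiety scales and follow-up interviews can also register deterioration. That is useful, but a mean can hide a few children who got worse, and it is not adverse-event collection.
- **No comparison of event counts between arms is announced.** The study is mainly descriptive, so the bias arises only if counts are reported by arm.

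It can also be said that the full protocol, the interview schedules, the time-point figure and the sponsor's procedures are not shown. That limits the finding to what the article describes, but does not remove it. The article states its detection route, and it brings in the sponsor's procedures for action once an event has been identified.

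**Conclusion.** The point holds as a design weakness worth correcting. It does not threaten the main feasibility and acceptability aims. Routine adverse-event enquiry, as described, is fourfold unequal between arms (8 against 2 occasions) and is absent from the 26 weeks after treatment, which is 84% of family-weeks when each arm is counted on its own clock. Counts by arm would mix risk with ascertainment, and a low count could not confirm that risks are minimal.

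The fourfold figure assumes that the agenda item covers control leaders; if it does not, the imbalance is larger. The 84% also assumes weekly control sessions.

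A reader might go further and infer that the trial will show a false excess of about 4 to 1 in recorded events. The documents do not support that as a prediction. They give no event rate, parents may mention at one session something that happened between sessions, and reactive routes may capture some events in either arm. The ratio measures opportunity and is not an expected result.

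**What to change.** 1. Add the same open question, on any unwanted events since last contact, to both arms' postal questionnaires at post-treatment, 12 and 26 weeks. Use the postal form and not the telephone interview. The blinded researcher makes those calls, and Randomisation and blinding already warns that parents may reveal their allocation. An answer given at the post-treatment call could unblind the same researcher for the two later ones.
2. Have the answers processed by staff other than the blinded assessor.
3. Report these uniformly collected events by arm, with the number of questionnaires returned and the weeks each one covers. The first interval may be shorter in control if its post-treatment assessment follows its own two sessions. List events found through supervision separately and do not pool the two sources.
4. State whether the supervision agenda item applies to control group leaders.
5. Report by arm the number of children rated in the bottom 3 points of the nine-point scale, beside the number of responders.

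Safeguarding and supervision stay as they are. The cost is one questionnaire item on a mailing already planned, some data handling by unblinded staff and one more table.
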